# Treatment of Persistent Postconcussion Syndrome With Repetitive Transcranial Magnetic Stimulation Using Functional Near-Infrared Spectroscopy as a Biomarker of Response: Protocol for a Randomized Controlled Clinical Trial

**DOI:** 10.2196/31308

**Published:** 2022-03-22

**Keywords:** concussion, mild traumatic brain injury, persistent postconcussion syndrome, repetitive transcranial magnetic stimulation, functional near-infrared spectroscopy, traumatic brain injury, TBI, brain injury, brain, symptom burden, mental health, quality of life, neuroscience, neurology

## Abstract

**Background:**

Approximately one-third of all concussions lead to persistent postconcussion syndrome (PPCS). Repetitive transcranial magnetic stimulation (rTMS) is a form of noninvasive brain stimulation that has been extensively used to treat refractory major depressive disorder and has a strong potential to be used as a treatment for patients with PPCS. Functional near-infrared spectroscopy (fNIRS) has already been used as a tool to assess patients with PPCS and may provide insight into the pathophysiology of rTMS treatment in patients with PPCS.

**Objective:**

The primary objective of this research is to determine whether rTMS treatment improves symptom burden in patients with PPCS compared to sham treatment using the Rivermead postconcussion symptom questionnaire. The secondary objective is to explore the neuropathophysiological changes that occur following rTMS in participants with PPCS using fNIRS. Exploratory objectives include determining whether rTMS treatment in participants with PPCS will also improve quality of life, anxiety, depressive symptoms, cognition, posttraumatic stress, and function secondary to headaches.

**Methods:**

A total of 44 adults (18-65 years old) with PPCS (>3 months to 5 years) will participate in a double-blind, sham-controlled, concealed allocation, randomized clinical trial. The participants will engage in either a 4-week rTMS treatment protocol or sham rTMS protocol (20 treatments). The left dorsolateral prefrontal cortex will be located through Montreal Neurologic Institute coordinates. The intensity of the rTMS treatment over the left dorsolateral prefrontal cortex will be 120% of resting motor threshold, with a frequency of 10 Hz, 10 trains of 60 pulses per train (total of 600 pulses), and intertrain interval of 45 seconds. Prior to starting the rTMS treatment, participant and injury characteristics, questionnaires (symptom burden, quality of life, depression, anxiety, cognition, and headache), and fNIRS assessment will be collected. Repeat questionnaires and fNIRS will occur immediately after rTMS treatment and at 1 month and 3 months post rTMS. Outcome parameters will be analyzed by a 2-way (treatment × time) mixed analysis of variance.

**Results:**

As of May 6, 2021, 5 participants have been recruited for the study, and 3 have completed the rTMS protocol. The estimated completion date of the trial is May 2022.

**Conclusions:**

This trial will expand our knowledge of how rTMS can be used as a treatment option of PPCS and will explore the neuropathophysiological response of rTMS through fNIRS analysis.

**Trial Registration:**

ClinicalTrials.gov NCT04568369; https://clinicaltrials.gov/ct2/show/NCT04568369

**International Registered Report Identifier (IRRID):**

DERR1-10.2196/31308

## Introduction

Concussion incidence has been rising among Canadians with the Ontario Physician Billing codes reporting an annual incidence of 1.2% of the population [1]. According to the Canadian Community Health Survey, over the last 2 decades, the number of concussions or other brain injury reports among Canadians is increasing, with 1 in 200 Canadians reporting a concussion or other brain injury to be their most disabling injury [2]. While many recover quickly from concussions, approximately one-third of patients with concussion have prolonged symptoms [3]. The symptoms that these individuals experience are collectively known as persistent postconcussion syndrome (PPCS), and can include cognitive, physical, and emotional impairments [4].

Transcranial magnetic stimulation (TMS) is a tool used to provide noninvasive electromagnetic induction through magnetic fields to the brain in conscious humans [5]. In general, single pulse TMS is used to explore brain function while repetitive TMS (rTMS) is used to change brain activity that lasts well beyond stimulation. rTMS has been shown to be an effective treatment for depressive disorders [6] as well as several other neurological conditions [7,8]. Furthermore, a recent systematic review showed that rTMS may be an effective treatment for patients experiencing PPCS, but studies with larger sample sizes are required to further support this evidence [9].

There is potential in using rTMS to improve symptoms for patients with PPCS, but the mechanism behind rTMS treatment for PPCS remains unknown. Recent studies have suggested that rTMS treatment modifies recovery pace and improves symptomatology [10,11]. Currently, very few studies have looked at biomarkers for rTMS treatment response in patients with PPCS. Our group previously conducted a 2-patient case study demonstrating how functional near-infrared spectroscopy (fNIRS) may be useful as a sensitive tool to predict treatment response to rTMS in patients with PPCS [12]. fNIRS is a noninvasive imaging technique that measures the differences in the absorption of local oxygenated and deoxygenated hemoglobin in the brain. The changes in cerebral tissue oxygenation are then used to monitor brain activity [13,14]. fNIRS has demonstrated comparability to functional magnetic resonance imaging for reliably detecting changes in cerebral vascular reactivity [15], and several studies have already examined the use of fNIRS for assessing concussions [15-17] and PPCS in adults [18]. Previous work assessing pediatric and adult patients with PPCS have shown reduced connectivity in both frontal and motor regions when compared to healthy controls during rest as well as during a finger tapping exercise and working memory task [18,19]. These findings are comparable to literature on functional magnetic resonance imaging, which has shown a reduction in connectivity in patients with mild traumatic brain injury during both resting state and task-based measures [20-22]. fNIRS has many advantages to being used in the clinical setting because of its portability and ability to replace other neuroimaging techniques that may be cost prohibitive.

The primary objective for this study is to determine if the application of rTMS treatment to the left dorsolateral prefrontal cortex (DLPFC) in patients with PPCS will significantly improve postconcussion symptoms using the Rivermead postconcussion symptom questionnaire (RPQ) compared to sham treatment. The second objective of the study is to explore the pathophysiology of rTMS response in participants with PPCS using fNIRS immediately following rTMS treatment and at 1-month and 3-month posttreatment follow-ups. An exploratory aim of the study is to determine whether rTMS treatment to the left DLPFC will improve quality of life, anxiety, depressive symptoms, fatigue, posttraumatic stress, and function secondary to headaches compared to sham treatment. We hypothesize that participants who show a clinically significant improvement in PPCS symptoms will also show an improved hemodynamic response in fNIRS recordings.

## Methods

### Study Design

This is a double-blind, sham-controlled, concealed allocation, randomized clinical trial. Recruitment will occur through 3 locations in Calgary, Alberta, Canada including the Calgary Brain Injury Program, the University of Calgary Sports Medicine Centre concussion clinic, and the Calgary Pain Program. The estimated study duration is from March 2021 to May 2022. Participant enrollment, fNIRS, and rTMS treatment will be completed by authors [name].

### Ethics Approval and Trial Registration

This study was approved by the University of Calgary Conjoint Health Research Ethics Board (REB15-1786). All participants will sign informed consent prior to study participation. This study has been registered with ClinicalTrials (NCT04568369).

### Participants

All participants will be between the ages of 18 and 65 years. The participants will meet the inclusion and exclusion criteria explained in this section. Inclusion criteria include a diagnosis of PPCS based on the International Classification of Diseases (ICD)-10 criteria for at least 3 months to a maximum of 5 years [23]. The ICD-10 states that PPCS must be followed by head trauma with loss of consciousness as well as any 3 of the following symptoms: feelings of unwellness (ie, headaches, dizziness, general malaise, and excessive fatigue or noise intolerance), emotional changes (ie, irritability, emotional lability, depression, and anxiety), difficulty concentrating or performing mental tasks or memory complaints, insomnia, reduced tolerance to alcohol, preoccupation with the above symptoms, and fear of permanent brain damage [23]. Current pharmacologic management will be maintained without change during the treatment study (ie, consistent use of triptans, opioids, tricyclic antidepressants, and antiseizure medications). Participants undergoing Botox treatment will undergo rTMS treatment 6-8 weeks following their injection, which is around the time of peak Botox efficacy [24]. Exclusion criteria comprise a history of prior TMS therapy, TMS-related contraindications (pacemaker, metallic implants, and large intracranial lesion), change in medication, and other neurological or mental health medical conditions such as structural brain disease, previous seizure, psychiatric disorders excluding depression and anxiety (eg, schizophrenia and bipolar disorder), liver or kidney disease, malignancy, uncontrolled hypertension or diabetes, and pregnancy.

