### Study Procedure

The study procedure is outlined in Figure 1. Prior to starting the study, participant and injury characteristics and questionnaires will be completed. Demographic information will be collected including age, sex, education level, and employment status. The participant characteristics collected will include headache history, concussion history, past medical history, medication use, and family medical history. Finally, injury characteristics will include length of loss of consciousness, length of posttraumatic amnesia, initial Glasgow Coma Scale, and imaging findings. The participants will be randomized to either active or sham rTMS. Once randomized, the participants will complete questionnaires and fNIRS. They will then complete 4 weeks (20 sessions) of treatment. Questionnaires and fNIRS will be repeated immediately following treatment and then at 1 month and 3 months post treatment.

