### Blinding and Randomization

The participants will be randomized to either active or sham rTMS treatment by a research assistant external to the study using sequentially numbered opaque concealed envelopes. All individuals involved in the study except the research assistant administering the rTMS will be blinded to the treatment protocol, and allocation will be concealed. Following study completion, the participants and study personnel will be unblinded. Once recruitment is completed, if rTMS treatment proves beneficial after a full statistical analysis, the participants in the sham groups will be offered active rTMS treatment.

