#### Statistical Analysis

The effect size of the RPQ score extrapolated from a similar study (*d*=0.77) [10] provided the basis for a power calculation performed with an alpha of .05, and 80% power suggested that 44 participants should be included in this study (22 per group). Anticipating a 20% attrition [10,22,55], 56 participants will be recruited for this study.

Descriptive statistics will be used to analyze baseline characteristics. A 2-way (treatment × time) mixed ANOVA will be used to assess whether any changes in clinical measurements and outcome parameters were the result of the interaction of type of treatment (real vs sham) and time. fNIRS data will also be analyzed using a 2-way mixed ANOVA where interregional coherence will act as the dependent variable, sham vs real TMS treatment will act as the between-subject variable, and brain region and assessment (ie, pre-TMS, post-TMS, 1-month follow-up, and 3-month follow-up) will act as the within subject variables. A *P* value of ≤.05 will be considered significant. A post hoc analysis will be used for exploratory measures. Simple effects testing using a Bonferroni correction will be performed when a significant group by time interaction is detected.

fNIRS data will be assessed to determine the location and magnitude of task-evoked changes in oxyhemoglobin, deoxyhemoglobin, and total hemoglobin at the left DLPC for each participant. Coherence of hemodynamic frequencies between major brain regions will also be quantified to observe brain connectivity during tasks as previous works have done [18,19]. Our group has previously attempted to decrease bias by restricting change in medication and other treatments throughout the trial [11]; however, it is unknown how some medications may influence rTMS and fNIRS data. Full patient characteristics, injury characteristics, and medication profile will be collected to better understand this bias.

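### PPCS may have lasted from 3 months to 5 years at entry, but the stated primary model has no term for duration, which costs precision at 22 per arm

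*Protocol article*

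**What the plan says.** The Participants section requires an ICD-10 diagnosis of PPCS meeting the "criteria for at least 3 months to a maximum of 5 years". The Abstract gives nearly the same window. As worded, the clock could start at injury, at symptom onset or at diagnosis.

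Under Blinding and Randomization, allocation is made "by a research assistant external to the study using sequentially numbered opaque concealed envelopes". No stratification factor is named, and the generation of the sequence is not described.

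For the clinical outcomes, Statistical Analysis says that a two-way "mixed ANOVA will be used to assess whether any changes in clinical measurements and outcome parameters were the result of the interaction" of treatment type and time. Baseline characteristics are to be summarised descriptively, and no covariate is named. The same section plans 22 per group from d = 0.77, alpha .05 and 80% power, with 56 recruited to allow for 20% attrition.

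On data collection, Study Procedure says that "injury characteristics will include length of loss of consciousness, length of posttraumatic amnesia, initial Glasgow Coma Scale, and imaging findings". Duration is not in that list, although concussion history is collected separately and could hold it. Statistical Analysis adds, in a remark about medication: "Full patient characteristics, injury characteristics, and medication profile will be collected to better understand this bias". It gives those characteristics no role in a model.

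**The concern.** The primary comparison is the treatment-by-time interaction, that is, the difference between arms in change over time. Any baseline factor that predicts change therefore acts directly on the tested term. Duration is a plausible factor of this kind. Follow-up runs about 4 months from baseline (4 weeks of treatment plus 3 months). That takes a 3-month case to 7 months, more than double, and a 60-month case to 64 months, an increase of under 10%.

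If the two kinds of case change at different rates without treatment, an unadjusted model puts that difference into the error term. In a trial with 22 per arm, the arms can also differ by chance in their mix of durations. At stake are power and the credibility of the estimate if the arms turn out visibly unequal. A covariate added after unblinding would be open to the charge of having been chosen for its result.

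**Working it through.** **1. The plan's own figure.** Inputs from Statistical Analysis: d = 0.77, alpha .05, power 80%, two equal arms. A two-sample t-test needs 21.56, so 22 per arm, one-sided, which gives the stated 44. Two-sided it needs 27.47, so 28 per arm. Attrition: 22 / (1 − 0.20) = 27.5, so 28 per arm and 56 recruited, as stated. With 22 per arm analysed, power is 80.7% one-sided and 70.4% two-sided. The article does not state sidedness. That is a separate matter, but it means there is little precision to spare. Two-sided power is used below.

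**2. Width of the window.** 60 / 3 = 20-fold.

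**3. Gain from adjustment.** The documents give no correlation r between duration and RPQ change, so 0.2, 0.3 and 0.5 are assumed. Adjustment multiplies the residual variance by 1 − r². The effective standardised effect becomes 0.77 / √(1 − r²), and an adjusted analysis of 44 × (1 − r²) participants is about as precise as an unadjusted one of 44. Power and type I error come from a simulation of 100,000 trials per setting, with 22 per arm and a two-sided 5% test. It compared a t-test on change with the same comparison adjusted for one baseline covariate. This simplifies the four-assessment ANOVA to a single change score.

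| r | 1 − r² | effective d | 44 × (1 − r²) | power unadjusted | power adjusted |
|---|---|---|---|---|---|
| 0.2 | 0.96 | 0.79 | 42.2 | 70% | 71% |
| 0.3 | 0.91 | 0.81 | 40.0 | 71% | 74% |
| 0.5 | 0.75 | 0.89 | 33.0 | 70% | 81% |

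Over all randomisations, type I error was 4.8-5.1% unadjusted and 4.9-5.0% adjusted.

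**4. Chance imbalance.** The difference between arms in a standardised covariate has SD √(2/22) = 0.30, with a 95% range of ±1.96 × 0.30 = ±0.59. The probability that it exceeds 0.5 SD in either direction is 2 × [1 − Φ(0.5 / 0.3015)] = 9.7%. With 28 per arm it is 6.1%. An imbalance of 0.5 SD shifts the unadjusted estimate by 0.5 × r. Within the roughly one trial in ten with an imbalance above 0.5 SD:

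| r | shift at 0.5 SD | share of 0.77 | type I error, unadjusted | power if imbalance is against rTMS: unadjusted | same, adjusted |
|---|---|---|---|---|---|
| 0.2 | 0.10 SD | 13% | 6.5% | 56% | 67% |
| 0.3 | 0.15 SD | 19% | 8.5% | 47% | 70% |
| 0.5 | 0.25 SD | 32% | 14% | 29% | 79% |

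**5. Form of the covariate.** A value fixed at baseline, entered only as a main effect, explains differences in a participant's average level. It leaves the treatment-by-time test unchanged. To help that test, it must enter with its interaction with assessment.

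**The case against.** The strongest case against the point has four parts.

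- *Randomisation already handles this.* It does on average. Natural recovery acts equally on both arms in expectation, and the P value and confidence interval allow for chance imbalance. A reader might infer that spontaneous recovery will be mistaken for a treatment effect. The documents do not support that: allocation is concealed, the control is sham, and the unadjusted type I error stays near 5%. The conditional figures in step 4 apply only to the minority of badly imbalanced trials.
- *The article is condensed.* Strata and covariates may be in a full protocol or SAP that is not shown. So it cannot be said that allocation was simple or unstratified, or that duration goes unrecorded. What remains is that the article does fix a model and its factors, and duration is not among them.
- *The size rests on assumptions.* It does. At r = 0.2 the gain is about one point of power. If half the participants were recent cases, r would be 0.5 × the gap in untreated change between recent and long-standing cases. Reaching 0.5 would then need a gap of a full SD (0.5 × 1 = 0.5).
- *The clinical premise is not stated.* Nothing in the article says that 3-month cases are still recovering or that 5-year cases are stable, and the 3-month minimum already selects persistent cases. Duration is therefore only plausibly prognostic.

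Stratifying the remaining envelopes is also tempting, but would help little. With completion due in May 2022 and about 4 months from baseline to last visit, the last participant would have entered around January 2022, before the article appeared in March 2022.

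**Conclusion.** The point holds as a recommendation on efficiency, not as an error that invalidates the trial. A wide entry window is paired with a stated model that ignores a baseline value already needed for eligibility. The expected gain in two-sided power at 44 analysed is about 1, 3 or 11 points for assumed correlations of 0.2, 0.3 and 0.5. The further benefit is protection in the roughly 10% of trials of this size where the arms differ by more than 0.5 SD in duration. These figures assume a linear relation with one change score and complete data on 22 per arm. The stronger conclusion, that the plan builds in a biased comparison, is not supported.

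**What to change.** - Define the start point of duration, either date of injury or date of PPCS onset, and use it for both eligibility and analysis. Record that date for every participant, including those already enrolled.
- Before unblinding, prespecify log duration and its interaction with assessment as covariates in the RPQ model, and likewise in the fNIRS coherence model. The log scale suits a 20-fold range.
- Keep the unadjusted ANOVA as a stated sensitivity analysis if comparison with the published plan is wanted.

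The cost is small. Little or no new data are needed, since eligibility already depends on duration. Each model loses one between-subject degree of freedom and, with four assessments, 4 − 1 = 3 within-subject degrees of freedom. If duration proves only weakly prognostic, little is gained.

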### Study Procedure

The study procedure is outlined in Figure 1. Prior to starting the study, participant and injury characteristics and questionnaires will be completed. Demographic information will be collected including age, sex, education level, and employment status. The participant characteristics collected will include headache history, concussion history, past medical history, medication use, and family medical history. Finally, injury characteristics will include length of loss of consciousness, length of posttraumatic amnesia, initial Glasgow Coma Scale, and imaging findings. The participants will be randomized to either active or sham rTMS. Once randomized, the participants will complete questionnaires and fNIRS. They will then complete 4 weeks (20 sessions) of treatment. Questionnaires and fNIRS will be repeated immediately following treatment and then at 1 month and 3 months post treatment.

**Figure 1 figure1:**
[figure not shown]
Study design protocol. DSM-5: Diagnostic and Statistical Manual of Mental Disorders, Fifth Edition; fNIRS: functional near-infrared spectroscopy; TMS: transcranial magnetic stimulation.

### Blinding and Randomization

The participants will be randomized to either active or sham rTMS treatment by a research assistant external to the study using sequentially numbered opaque concealed envelopes. All individuals involved in the study except the research assistant administering the rTMS will be blinded to the treatment protocol, and allocation will be concealed. Following study completion, the participants and study personnel will be unblinded. Once recruitment is completed, if rTMS treatment proves beneficial after a full statistical analysis, the participants in the sham groups will be offered active rTMS treatment.

### TMS Protocol

The participants will engage in a 4-week treatment protocol (20 treatments). This was chosen as it reflects prior depression, PPCS, and migraine protocol durations [25-27]. A standardized atlas brain with Montreal Neurologic Institute coordinates will be used for navigation. rTMS treatment will be to the left DLPFC and will be located through Montreal Neurologic Institute coordinates (-50, 30, 36) [28]. The resting motor threshold will be determined using electromyography electrodes attached to the right abductor digiti minimi muscle and a TMS stimulation coil placed over the left motor cortex, as previously described by Stilling et al [11]. The intensity of the rTMS will be 100%-120% of resting motor threshold amplitude, with a frequency of 10 Hz, 10 trains of 60 pulses per train (total of 600 pulses) and intertrain interval of 45 seconds. In the sham condition, a sham coil will be applied to the scalp after the resting motor threshold is determined. Recent studies exploring rTMS implementing a 100%-120% resting motor threshold amplitude as a treatment for PPCS have been successful for patient retainment and treatment success [25,27,29,30]. Our group has previously used an intensity of 70% resting motor threshold in a similar patient population [11]. This protocol will use 120% resting motor threshold to attempt to achieve a greater neurophysiological effect [31]. Furthermore, previous studies treating posttraumatic headache and migraine show benefit using a frequency of 10 Hz, 600 pulses, and intertrain interval of 45 seconds, suggesting this protocol would also be beneficial in PPCS [32-35]. The sham coil will produce sounds and vibration similar to the real rTMS coil but will not produce any effective stimulation. This blinding method has been demonstrated to be effective in previous sham TMS studies [36].

